# *Ask*: a health advocacy program for adolescents with an intellectual disability: a cluster randomised controlled trial

**DOI:** 10.1186/1471-2458-12-750

**Published:** 2012-09-07

**Keywords:** Intellectual disability, Health advocacy, Adolescent, School-based intervention, Doctor patient relations, Primary health care, General Practitioner, Health diary, Health check

## Abstract

**Background:**

Adolescents with intellectual disability often have poor health and healthcare. This is partly as a consequence of poor communication and recall difficulties, and the possible loss of specialised paediatric services.

**Methods/Design:**

A cluster randomised trial was conducted with adolescents with intellectual disability to investigate a health intervention package to enhance interactions among adolescents with intellectual disability, their parents/carers, and general practitioners (GPs). The trial took place in Queensland, Australia, between February 2007 and September 2010. The intervention package was designed to improve communication with health professionals and families’ organisation of health information, and to increase clinical activities beneficial to improved health outcomes. It consisted of the Comprehensive Health Assessment Program (CHAP), a one-off health check, and the *Ask Health Diary*, designed for on-going use. Participants were drawn from Special Education Schools and Special Education Units. The education component of the intervention was delivered as part of the school curriculum. Educators were surveyed at baseline and followed-up four months later. Carers were surveyed at baseline and after 26 months. Evidence of health promotion, disease prevention and case-finding activities were extracted from GPs clinical records. Qualitative interviews of educators occurred after completion of the educational component of the intervention and with adolescents and carers after the CHAP.

**Discussion:**

Adolescents with intellectual disability have difficulty obtaining many health services and often find it difficult to become empowered to improve and protect their health. The health intervention package proposed may aid them by augmenting communication, improving documentation of health encounters, and improving access to, and quality of, GP care. Recruitment strategies to consider for future studies in this population include ensuring potential participants can identify themselves with the individuals used in promotional study material, making direct contact with their families at the start of the study, and closely monitoring the implementation of the educational intervention.

**Trial Registration Number:**

ClinicalTrials.gov Identifier: NCT00519311

## Background

Over half a million Australians have an intellectual disability
[1]. In this population there are high levels of unrecognised disease, inadequate health screening and promotion, and premature death
[2]. We and others have provided some useful information on health checks as a way to improve the health of adults with intellectual disability
[3-11]. This project moves on to address another need - the health of adolescents with intellectual disability. The potential for enhancing life-long health and well-being is high in this group, but evidence is lacking.

The few published studies show there are many unrecognised health problems in adolescents with intellectual disability
[12,13]. In one 40% of students examined were found to have previously unidentified health issues, with vision and hearing defects being the most prevalent
[12]; obesity, orthopaedic problems, dental caries, incomplete immunisations, ENT pathology and skin conditions were also very common
[12,13]. Of particular importance is epilepsy, with a prevalence of 20% in this group, as polypharmacy and antiepileptic medication side effects are common and often unrecognised
[10,12,14]. During adolescence mental health issues are also important, particularly for those with intellectual disability, whose prevalence of psychiatric disorders is 3–4 times higher than the norm
[15-17].

Central to understanding the health of this population are the difficulties they face with communication and recall, which can contribute to the poor reporting of problems
[18-20]. As they become more independent from their parents they also face losing the support of their specialist paediatric services and possibly continuity of medical care from their family General Practitioner (GP). This makes it even more important that strategies to minimise the barriers to good healthcare are investigated; these include improved health information systems (records and history taking), health checks, high quality advocacy and education of carers and healthcare providers
[18].

A systematic review of the impact of health checks for people with intellectual disability included 38 publications, none of which focussed on the health of adolescents
[10]. However there is now substantial trial evidence that adults with intellectual disability who receive health checks experience substantial increases in clinical activities conducive to beneficial health outcomes
[9]. GPs perceive a health check in adults as a structured and comprehensive approach to the detection of medical problems as well an aid in overcoming communication problems between the doctor and the person with a disability
[21]. Taken together with the high levels of unmet health need among adolescents with intellectual disability, directly assessing the impact of health checks among them makes good sense.

While health checks are a one-off tool designed to increase GPs’ attention to the health needs of individuals with intellectual disability, it is also desirable to ensure longer-term improvement in healthcare advocacy than is achievable using a one-off health check. To this end we have designed and tested among adults a personalised hand-held health record, the *Ask Health Diary*. It contains a record of a client’s personal details, including means of communication, contacts for medical and allied health practitioners, and a medical record of diagnoses, operations, medications, immunisations, allergies, family history of disease and medical consultations
[8]. It aims for longer-term enhancement of communication, health records and history taking, and education of carers and healthcare providers. In pilot studies we found that adults with intellectual disability, parents and paid carers who used the diary considered themselves to be better advocates, and that the diary was acceptable for use. They reported improvements in communication, in relationships with their GPs and in organisation of their health information.

The Health Intervention Package is a combination of a health check, the Comprehensive Health Assessment Program (CHAP), and a personalised hand-held health record, the *Ask Health Diary*. The aims of the study are to determine: (1) if adolescents with intellectual disability using this package receive better healthcare (e.g., health screening) and improved health outcomes; (2) if using this package improves health advocacy by adolescents with intellectual disability and their parents/carers in the context of visits to the GP; and (3) if this package is acceptable to adolescents with intellectual disability, their families, their teachers, and their GPs.

The aim of this paper is to describe the pilot study and the trial design of the full randomised controlled trial; to describe which strategies were successful and which were not; and to explore how future projects could be implemented more effectively.

## Methods/Design

### Pilot study

The pilot study examined the implementation of the health intervention package (CHAP health check and *Ask Health Diary*) in adolescents with intellectual disability in one special school
[22]. This pilot involved recruitment of 37 students aged 13 years and older with intellectual disability, their parents/carers, the principal and 6 teachers. To introduce the project, we held a presentation at the school; recruitment was assisted by the school principal using telephone and postal communications. In order to actively involve the teachers, the research team’s educational expert met with them and developed curriculum plans including teaching strategies for the *Ask Health Diary*. The diary was distributed to adolescents and used as the basis of a health educational program in six classrooms during the third term of 2004. At the end of the term the Health Intervention Package was taken home to the adolescents’ parents/carers. The family commenced using the *Ask Health Diary*, provided details of the adolescents’ medical history in the first part of the CHAP tool (described below) and organised a health check by their child’s GP. Interviews were conducted with teachers, parents/carers and adolescents before and after receipt of the Health Intervention Package to evaluate its acceptability and efficacy.

A response rate of 72% from the parents/carers was achieved through the support of Education Queensland, the adolescents, their parents/carers, teachers and GPs, and most especially the principal. Results indicated the intervention package was acceptable to all 37 students with intellectual disability, their parents/carers and the six teachers in this school and could be used by adolescents with heterogeneous educational needs. After consultation with Education Queensland, special education teachers, principals and heads of Special Education Schools and Special Education Units, it was clear that to enable use of the new health education material there was a need to fund the schools to relieve the teachers from routine classroom duties. This relief time would allow the teachers to formulate educational strategies for implementation of the *Ask Health Diary* into the teaching plan and enable them to participate in the research interviews. These findings informed the design of the randomised controlled trial as described below.

### Trial design

The study is a parallel group cluster randomised controlled trial testing the usefulness of a health intervention package. The study was conducted among adolescents with intellectual disability in South East Queensland, Australia, between February 2007 and September 2010. The package combines the CHAP health check, the *Ask Health Diary* and the *Ask Project Curriculum Strategy Booklet.* The timeline for the study as proposed is shown in Figure
1.

**Figure 1 F1:**
[figure not shown]
Original Project Timeline.

Ethics approval was granted by both the University of Queensland Behavioural and Social Sciences Ethical Review Committee (Clearance No: 2004000081) and the Queensland Government Department of Education and the Arts (File No: 550/27/424).

### Participants

Participants were drawn from Special Education Schools (SESs) and Special Education Units (SEUs) in Southern Queensland. Children were eligible to participate in the study if they had been assessed by Education Queensland to have an intellectual disability, were aged 10 to 18 years as at 1 January, 2006, and were registered at Education Queensland SESs or SEUs located in Southern Queensland. In Queensland, children who have an intellectual disability may receive their education in a segregated special school for children who have a disability (SES) or in a special education unit or class that is on the campus of a mainstream primary or secondary school (SEU). Students who attend a special school have significant intellectual disabilities and/or multiple disabilities, and usually require specialist teaching and therapy services that support an individualised education program. A small number of these special schools are designated as “High-Support Needs Special Education Schools” and have the staff and specialised facilities required for children with profound disabilities. Students who attend a special education unit in a primary or secondary school may have a range of disabilities, and usually access the mainstream curriculum and receive specialist teaching and therapy services. The choice of placement options for students with disabilities can be influenced by a range of factors, such as parent choice and education options available in the local area.

### Recruitment

Under the terms of the ethical clearance provided by Education Queensland it was necessary to obtain consent from the relevant principals/heads before research could be conducted, but before this could be obtained, the following process was undertaken:

• *Central executive level contact*. Although participant recruitment did not occur at this level, the purpose of this executive level contact was to: (a) secure direct support from a Senior Executive for the study (as indicated by a written letter of support); (b) seek advice on appropriate strategies to recruit SESs and SEUs within Southern Queensland; and (c) access the names and contact details of schools. Support was obtained for the study to be conducted in State schools. Catholic and some other independent schools were also approached, but their recruitment was considered too difficult in the time frame.

• *Regional and district level contact*. The chief investigator contacted the district directors of all schools in Southern Queensland to: (a) provide information about the study; (b) seek district-level support for the study; and (c) obtain the names and contact details for Principal Education Officers (Student Services) in each district.

• *Principal Education Officers – Student Services (PEOs).* The research officers responsible for recruitment then contacted by telephone all of the PEOs in Southern Queensland, which was followed up by an emailed information package. The purpose of this contact was to: (a) provide information about the study; (b) seek PEO support for the study; and (c) identify opportunities to discuss the study with principals and Heads of Special Education Services of the SESs and SEUs in each PEO’s jurisdiction.

• *Principals and Heads of Special Education Services (HOSES).* The project manager and/or the research officer responsible for recruitment then contacted Principals of the SESs and HOSES of the SEUs by telephone to introduce the study. The purpose of initial telephone contact was to (a) determine the eligibility of each SES/SEU to participate in the study; and (b) identify opportunities for speaking to parents/carers about the study. The recruitment officer then arranged to visit all interested schools to describe the project to teachers. The *Ask Project Curriculum Strategy Booklet* was made available on the web for staff to peruse.

If schools agreed to participate, information sheets and consent forms were provided for distribution to parents/carers of possible participants via school newsletters or communication books. As some of the parents of these adolescents also had disability and literacy problems, a DVD was produced to describe the program and was distributed to families.

The name and contact details of the adolescent’s usual GP was provided by the parent/carer of each participant at baseline. A brief introductory letter describing study objectives, research design and data collection process, and the type and level of participation required was sent to each nominated GP, followed by a phone call from research staff. A consent form and detailed information sheet was faxed to doctors; this included information on how the GP could claim a government funded fee for providing a comprehensive health check. On completion of GP recruitment a thank you letter was sent to consenting GPs advising them of the participants who had nominated them as their usual GP.

### Sample size

We estimated there would be 2,403 adolescents aged 13 to 18 years and registered at SES or SEU, based on Education Department data from the year prior to study commencement. Approximately 80% of these adolescents would have intellectual disability; meaning approximately 1900 students would be eligible for the study. We estimated that around 60% of schools would choose to participate in the study, and that within each school 95% of eligible individuals would participate. Consequently we expected to have a total sample size of around 1,000 adolescents (80% x 60% x 95% of 2403). We estimated participants would be grouped into around 50 clusters (assuming that an average of 20 (SD = 7.5) adolescents with intellectual disability would attend any one school). Thus we expected that each of the intervention and usual care groups would comprise 500 students from 25 schools.

One of the primary outcomes of interest is detection of vision or hearing impairment, which previous studies have shown has a current rate of around 10% in this population
[12,13]. With an assumed intra-class correlation coefficient (ICC) of 0.03, the design effect for this analysis is 1.57, without consideration of matching. On this basis, the study would have 90% power to detect an increase in the detection of vision impairment to 19% due to the intervention, at the 5% level of significance. For a condition with a current impairment rate of 20%, the study will have 90% power to detect an improvement to around 30% through the intervention. The matched-pairs design will have greater power, depending on the within-pair correlations, so the above estimates are conservative. The assumption of a maximum 0.03 for the ICC is plausible, based on a reported ICC (0.01) in an adult population
[7]. For analyses of major subgroups, e.g. examining increases within adolescents with Down syndrome, an estimated 25% of the sample distributed across clusters, the study would have 80% power to detect increases of 10% to 24%, or 20% to 37%.

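### The planned inputs give about 83% power for 20% to 30%, not 90% (90% needs about 31%), and the claim that the power figures are conservative is not demonstrated

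*Protocol article*

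**What the plan says.** All of this is in the protocol article, Methods/Design, Sample size.

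- Size: "each of the intervention and usual care groups would comprise 500 students from 25 schools".
- Cluster size: the plan gets about 50 clusters by "assuming that an average of 20 (SD = 7.5) adolescents with intellectual disability would attend any one school".
- Clustering: "With an assumed intra-class correlation coefficient (ICC) of 0.03, the design effect for this analysis is 1.57, without consideration of matching".
- Power at a 10% baseline: 90% for a rise to 19%, at the 5% level.
- Power at a 20% baseline: "the study will have 90% power to detect an improvement to around 30% through the intervention".
- Matching: the matched-pairs design is expected to have more power, to a degree that depends on the within-pair correlations, "so the above estimates are conservative". No value for that correlation is given.
- ICC: 0.03 is described as a maximum and set against 0.01 reported in an adult population.
- Down syndrome subgroup (25% of the sample): 80% power for 10% to 24% or 20% to 37%.

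**The concern.** The two 90% statements share the same sample size, ICC and significance level, so one calculation should give both. It gives the first but not the second. The discrepancy is in the optimistic direction, and the next sentence tells the reader that the figures err on the safe side. Someone using this section to judge a null result on an outcome with a baseline near 20% would assume a type II error of 10% for a rise to 30%, when the planned inputs imply about 17%.

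The design effect raises a related question: a cluster-size SD is given but does not enter the calculation.

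**Working it through.** **Inputs (Sample size section).** n = 500 per arm; mean cluster size m = 20, SD 7.5; ICC = 0.03; alpha = 0.05. Whether the test is one- or two-sided is not stated; two-sided is assumed here and checked below.

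**Design effect as stated.** 1 + (20 − 1) × 0.03 = 1.57, which reproduces. Effective n = 500/1.57 = 318.5 per arm.

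**Power formula.** Normal approximation for two proportions, with pooled variance under the null and p̄ = (p1 + p2)/2:

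z = [(p2 − p1) − 1.96 × √(2p̄(1 − p̄)/n)] / √([p1(1 − p1) + p2(1 − p2)]/n), power = Φ(z).

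*10% to 19%:* (0.09 − 1.96 × 0.02790)/0.02767 = 1.276, power 89.9%. Stated 90%; reproduces.

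*Down syndrome subgroup:* 125 per arm, 5 per school, design effect 1 + 4 × 0.03 = 1.12, effective n = 111.6. Power is 79.9% for 10% to 24% and 80.8% for 20% to 37%. Stated 80%; both reproduce.

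*20% to 30%:* (0.10 − 1.96 × 0.03431)/0.03409 = 0.961, power 83.2%. Stated 90%; does not reproduce.

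**What would give 90%.** Solving for p2 gives 31.2%. At 30.5%, the top of the range that rounds to 30%, power is 86.4%; at 31% it is 89.2%. Exactly 30% with 90% power needs 392 effective students per arm, and 392 × 1.57 is about 615 per arm.

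**Other test versions for 20% to 30% at 318.5 effective per arm**

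| Version | Power |
|---|---|
| Unpooled variance | 83.5% |
| Arcsine | 83.3% |
| Continuity-corrected | 80.8% |
| t, 48 df | 82.0% |
| One-sided 5% | 89.9% |

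The one-sided test matches here, but it puts 10% to 19% at 94.4%. It is therefore not the rule behind the other figures.

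**Allowing for the stated SD.** CV = 7.5/20 = 0.375. The usual formula gives 1 + [(1 + 0.375²) × 20 − 1] × 0.03 = 1.654, so effective n = 302.2 per arm. Power is 88.3% for 10% to 19% and 81.2% for 20% to 30%, and the rate detectable from 20% with 90% power is 31.5%.

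This is an upper figure, because a mixed model weights schools more efficiently. Under such weighting, a school of m students contributes m/(1 + (m − 1) × 0.03) effective students, which is 12.74 at m = 20. A second-order correction for variance 7.5² = 56.25 is −½ × 0.01504 × 56.25 = −0.42, giving 12.32. The design effect is then 20/12.32 = 1.62, and the powers are 89.0% and 82.0%.

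**How much matching would have to do.** The design effect splits as 0.97 + 20 × 0.03 = 0.97 + 0.60. If matching removes a fraction r of the between-school variance, it becomes 0.97 + 0.60(1 − r). Reaching 90% for 20% to 30% needs 500/392 = 1.276, so r is about 0.49, with equal school sizes and no loss of degrees of freedom.

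**The case against.** **The text says around 30%, not exactly 30%.** This stands in part. Measured on the detectable rate, the gap is only about one percentage point, so it looks like loose rounding and not a wrong method. But the other detectable rates (19%, 24%, 37%) are right to the nearest point, and here one point is worth about seven points of power.

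**The sample size was itself rounded down.** The stated product is 0.80 × 0.60 × 0.95 × 2403 = 1,096, or 548 per arm. At design effect 1.57 that gives 86.4% for 20% to 30% and a detectable rate of 30.6%. This narrows the gap but does not close it, and the plan fixes its groups at 500.

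**The ICC was set cautiously.** This is the strongest point. At the reported 0.01 the design effect is 1 + 19 × 0.01 = 1.19, and power is 91.9% for 20% to 30% and 96.1% for 10% to 19%. The plan, however, states its powers at 0.03 and draws the word conservative from matching. The margin tempers the criticism without making the 90% follow from the inputs used.

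**Matching can add power.** True, and pairing within school type and location, on lists ranked by expected size, makes some gain plausible. The article does say that the gain depends on the correlation. What is missing is any value for it.

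**Readings that go too far.** A reader might infer that matching will cost power because a paired t-test on 25 pairs has only 24 degrees of freedom. The Quantitative analysis section plans individual-level mixed-effects models allowing for cluster and matching effects, not that test, so power figures built on it do not describe this trial. A reader might also infer that the main sample-size justification fails. It does not: the vision or hearing scenario, 10% to 19%, holds at 1.57 and stays close to 90% after allowing for unequal schools.

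**Conclusion.** The point holds, at minor to moderate severity. One of four stated power figures does not follow from the plan's inputs: about 83% for 20% to 30%, a type II error of about 17%; 90% is reached at about 31%. Allowing for the stated cluster-size SD lowers 20% to 30% to about 81–82% and 10% to 19% to about 88–89%.

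The claim of conservatism is not demonstrated. It rests on a correlation that is not given, and it leaves out cluster-size variation, which works the other way. The documents do not show that the claim is false, since the ICC assumption contains real slack.

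These results assume a two-sided 5% test, the normal approximation, 500 per arm and ICC 0.03. They concern planned power only, not power at the numbers actually recruited.

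**What to change.** In the Sample size section:

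1. Replace the 20% baseline statement with: 83% power for 20% to 30%, or 90% power for 20% to about 31%. State that the 5% test is two-sided, if it is.
2. Quote alongside it the powers that allow for the cluster-size SD of 7.5. At a design effect of up to about 1.65, these are about 88% for 10% to 19% and 81% for 20% to 30%.
3. Replace the statement that the estimates are conservative with a conditional one: matching may add power, depending on the within-pair correlation. If the authors want to claim a margin, the ICC is the better ground, as 0.03 against 0.01 reported, with the power at each value shown.

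The cost is wording only. The sample size, design and analysis are unchanged, and the quoted powers become slightly less favourable.
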